### Data collection

Mixed methods of data collection, quantitative and qualitative, are used. There were no specific plans to promote participant retention to avoid biasing the trial outcomes that the cascade of cares for contact screening and management. The study reimburses participant’s transportation in case for safety reasons only.

#### Quantitative data

Other than the facility registers, study-specific source documents are used. The data for the primary and secondary objectives are collected by the TB focal person in the health facilities and community health workers in the community. There is one research assistant assigned to each cluster health facility who enters data onto tablets using the Research Electronic Data Capture (REDCap) mobile application version 4.9.1, 6 February 2020. Patients’ cost data are collected by research assistants in the REDCap mobile application using an adapted version of the patient cost tool developed by the WHO [39]. At the health system level, data are collected through literature, source documents from the Ministry of Health, primary expenditure analysis, and procurement records by the cost analysis researchers.

#### Qualitative data

The data for the qualitative assessment is collected by the social researchers through in-depth interviews and focus group discussions in English, French, or local language with the help of a local qualitative research assistant. Participants’ confidentiality and privacy are respected throughout the study. During the baseline phase of the study, a qualitative assessment of social determinants has been performed to identify the perceptions of TB, prevention for child contacts, and obstacles for treatment, acceptability, and feasibility of the proposed intervention. Focus group discussions have been organized with TB patients and in-depth interviews have been conducted with health staff, facility managers, CHW, and community leaders. During the implementation phase, data on concurrent acceptability is assessed through periodic supervision meetings of the CHW. A second qualitative assessment will be performed at the end of the intervention focusing on the acceptability and lessons learned. These activities are planned in both models of care implemented in the study.

#### Process data

In the baseline phase, sites were assessed in terms of quality of data collection in the registers and specific practices that would require adjustments for study organization of those sites. During the implementation phase, recruitment logs are filled in by research assistants to document study screening and enrolment process with reasons of refusal.

### Data management

A central data manager coordinates with local data managers to ensure the data entry and verification according to a Data Management Plan. There are three levels of data checking and quality control: at data entry using restricted value set or compulsory fields, at country-level data management running weekly checks, and at central-level data management with a monthly consistency data check. The collected data is anonymized by the use of unique study identification numbers and followed by the investigators through a dashboard system developed at the central level. The tablets used for the study are password-protected and have an individual identification for each research assistant. The tablet data is encrypted when sent to the server. The study database is on a web-based platform provided by REDCap [40, 41], protected by password, encrypted, and hosted at the Institut de Recherche pour le Development in Montpellier, France. The back-up of the database is done on a daily basis on the server of the Institut de Recherche pour le Development in Montpellier.

### Quality management

Each country research team is composed of one study coordinator, one clinical research assistant, and 8 research assistants. All staff is trained on good clinical practices, protocol, and study standard operating procedures. Training of the country research teams took place before the baseline phase and was done by the central research team. CHW were selected based on criteria regarding their education, experience with community activities, and acceptability by the community and capacity for study activities. The site teams (TB focal person, TB nurse, CHW, and safety monitor) were trained before the intervention phase by the country research teams. Each facility cluster has a clinician safety monitor trained to consult children with tolerability complaints and report adverse events. Standard operating procedures, country-specific manuals of procedures (to take into account the implementation specificities of each country), and a quality management plan were developed by the central research team. Clinical research assistants perform internal data monitoring from the eCRF against source documents on a monthly basis, and central site monitoring is done every 3–4 months. In addition, the sponsor performs a yearly site monitoring.

The study is overseen by a steering committee involving all investigators including representatives of the national TB program with monthly calls to discuss study inclusions, challenges, and decisions on study implementation and a scientific advisory committee composed by experts in the field of pediatric tuberculosis and randomized controlled trials with meeting twice a year to discuss study progress, challenges, and safety review. A country community advisory board is constituted to give guidance on the implementation of the community activities and support the study team on patient information and communication.

### Statistical analysis

#### Primary analysis

The denominator for the analysis of the primary endpoint is the number of child contacts < 5 years and HIV-infected 5–14 years declared by the index case at the facility during the inclusion visit. Since discrepancies can be expected between what is declared by the index case and what is observed during contact screening, a sensitivity analysis will be performed using as denominator the number of children < 5 years of age and HIV-infected children of 5–14 years of age identified during the screening. An additional sensitivity analysis will be performed including only participants that followed all study procedures (per-protocol approach) among the declared and then enrolled child contacts. Dropping out of the cascade of cares and potentially being lost to follow-up can be the consequence of the models of care under evaluation. Therefore, lost to follow-up will be kept in the primary outcome analysis. They will be removed from the sensitivity per-protocol analysis.

A generalized linear mixed model with a binomial distribution and logit link function will be used to perform individual-level analysis adjusting for clustering. The regression model will include the fixed effect of treatment assignation and country and one random-effect for the cluster. A degree-of-freedom correction will be applied (between-within method) to deal with the type I error inflation due to the small number of clusters. The primary analysis will focus on the difference between the two study arms adjusted for country, and a secondary analysis will add an adjustment for unbalanced factors (urban/rural, district size) identified in the baseline assessment. For the analysis of the secondary outcomes, a similar mixed model will be used with the same random effects and correction method, focusing on each endpoint of the cascade of care for initiation and completion of TPT and each endpoint of the cascade of care for TB detection. The same model will be applied for the sensitivity analyses.

The proportion of children notified in the facility TPT register among all notified cases during the intervention period will be compared between the two models of care and will also be compared with the same proportions before intervention for the same time period (data collected during the baseline assessment). The proportion of confirmed TB among all pediatric notified cases and the proportion of treatment completion will also be compared between the two models and with the pre-intervention period.

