**Methods/design:**

This multicenter parallel open-label cluster randomized controlled trial is composed of three phases: I, baseline phase in which retrospective data are collected, quality of data recording in facility registers is checked, and expected acceptability and feasibility of the intervention is assessed; II, intervention phase with enrolment of index cases and contact cases in either facility- or community-based models; and III, explanatory phase including endpoint data analysis, cost-effectiveness analysis, and post-intervention acceptability assessment by healthcare providers and beneficiaries. The study uses both quantitative and qualitative analysis methods. The community-based intervention includes identification and screening of all household contacts, referral of contacts with TB-suggestive symptoms to the facility for investigation, and household initiation of preventive therapy with follow-up of eligible child contacts by community healthcare workers, i.e., all young (< 5 years) child contacts or older (5–14 years) child contacts living with HIV, and with no evidence of TB disease. Twenty clusters representing TB diagnostic and treatment facilities with their catchment areas are randomized in a 1:1 ratio to either the community-based intervention arm or the facility-based standard of care arm in Cameroon and Uganda. Randomization was stratified by country and constrained on the number of index cases per cluster. The primary endpoint is the proportion of eligible child contacts who initiate and complete the preventive therapy. The sample size is of 1500 child contacts to identify a 10% difference between the arms with the assumption that 60% of children will complete the preventive therapy in the standard of care arm.

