## Background

Tuberculosis (TB) is an infectious disease causing incident cases of disease in around 10 million people worldwide in 2018 [1]. The World Health Organization (WHO) estimated that 11% of the TB cases in 2018 were in children (< 15 years). However, a modeling study has estimated that the pediatric caseload in high-burden countries is as high as 15–20% of all TB cases [2]. The mortality rate in undetected untreated children is estimated to be 21.9% for children of all ages and rises to 43.6% in young children of less than 5 years [3]. Improving case detection and treatment of this high-risk group of young children is particularly challenging due to diagnostic limitations and clinical overlap with other common severe diseases of infants and young children in resource-limited settings.

Research has consistently shown that TB disease in young children usually occurs soon after exposure and infection, that the risk of disease if infected is high, and that TB preventive therapy (TPT) can significantly reduce the risk of disease following exposure and infection [4]. A meta-analysis reported that 10% of young child contacts had TB disease at the time of screening, and 35% had evidence of infection [5]. A recent individualized participant meta-analysis found that the effectiveness of tuberculosis preventive treatment (TPT) was 63% (95% CI 53–70%) among all exposed children and 85% (95% CI 80–89%) among those with evidence of infection [4]. Therefore, the rapid identification and management of exposed children in the households of TB disease cases is a critical opportunity to detect, treat, and prevent TB. Although recommended for decades, household child contact screening and TPT have been poorly implemented in high-burden and resource-limited countries. For many years, children were considered lower priority due to being less infectious and therefore contributing less to TB transmission than adults [6].

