## Methods

### Study objective and endpoints

The primary objective of this study is to compare the proportion of household child TB contacts eligible for TPT who initiate and complete TPT under a facility-based standard of care and under a decentralized community-based intervention model of care for contact screening and management.

The corresponding primary endpoint is the proportion of child TB contacts < 5 years of age and HIV-infected children of 5–14 years of age who are declared by the index case and who initiate and complete the TPT.

The secondary objectives compare the aforementioned models in terms of (i) cascade of care of TPT initiation and completion in child contacts < 5 years or HIV-positive children 5–14 years; (ii) cascade of care for TB detection and treatment in all included contacts; (iii) tolerability and adherence in children initiated on TPT; (iv) acceptability and feasibility of the two models by the parents/guardians, health personnel, and community; (v) the effect of the community-based intervention on the number of adult contacts diagnosed with TB; and the cost-effectiveness. The number of children and adults diagnosed with TB and the number of children initiated on TPT will be also compared before and after the intervention.

The secondary endpoints of the study are presented in Table 1.

**Table 1 Tab1:** Secondary endpoints of the CONTACT study

General secondary endpoints	Detailed secondary endpoints
Cascade of care for the initiation and completion of TPT of child contacts < 5 years or HIV-infected 5–14 years and reasons of dropouts at different steps of the cascade	Number of screened children and proportion of children screened among child contacts < 5 years or HIV-infected 5–14 years declared by the index case
	Proportion of children potentially eligible for TPT: TB disease excluded
	Proportion of children eligible for TPT after exclusion of contraindication to TPT
	Proportion of children started on TPT among those eligible for TPT
	Proportion of children who did not complete TPT among those started on TPT and reasons of interruptions
Cascade of care for TB detection of child contacts	Proportion of children with symptoms suggestive of TB: presumptive TB
	Proportion of presumptive TB cases investigated for TB
	Proportion of children diagnosed with TB
	Proportion of children with TB diagnosis who are started on TB treatment

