### Sample size calculation

For the sample size calculation, we used an estimated 60% completion rate among the eligible children in the facility-based arm based on a recent systematic review [35] and a 10% difference in the community-based arm, considered to be the minimal clinically relevant difference. We considered a cluster coefficient variability of 50% based on the variation in the number of bacteriologically confirmed index cases between the 20 clusters in the year prior to the intervention. An intra-cluster correlation of 0.01 was used. With these parameters, we would need to include at least 1500 declared child contacts by the index case who would be eligible to the TPT to have a power of 85%. With a minimum of 1500 enrolled child contacts, we could maintain at least 80% of power to detect a difference of 10% in the primary outcome between the two arms assuming the proportion with the primary outcome in the control arm ranges from 60 to 70% and of the cluster coefficient variability varies from 50 to 70%. The type I error rate *α* is conventionally fixed at 0.05%. Based on national household statistics per country [36–38], we make the hypothesis of one child under 5 years per household. Looking at the index case TB registrations in the year prior to the intervention, we estimate that it would be possible to include 1500 contact children in a 15-month period. Research assistants in each cluster supervised that all bacteriologically confirmed index cases registered in the NTP treatment register were screened for study eligibility to achieve adequate participant enrolment to reach sample size.

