### Challenges

This is an implementation research which is highly dependent on the health system policy and organization. One of the many challenges to be taken into account is the change of the country guidelines during the implementation of the protocol as these changes require most of the time a protocol amendment with implications on study procedures and organization. Other challenges are related to shortages of TB medication, stock-outs of Xpert MTB/RIF cartridges that affect the identification of bacteriologically confirmed index cases at facility level and staff availability or turn over. The 3RH and 6H TPT drugs were provided by the study to prevent the risk of shortage. One cluster in Cameroon had to be changed after approval of the study protocol due to an unanticipated concurrent community-based intervention that could bias the study outcome measure. Additionally, in both countries, following the request from the NTP that TPT should be initiated by a nurse, the implementation of the intervention package could not rely on CHW only as initially planned and has to involve facility nurses moving to patients’ household. The same applies to HIV testing that cannot be done by trained CHW in Cameroon.

Constant communication with the CaP TB program team and the NTP team at higher and lower levels is crucial to anticipate any operational issue and find solutions to ensure the continuity of study activities according to the protocol. It also reinforces the level of ownership by the NTP and prepares the future scale-up of the intervention. The cost-effectiveness and qualitative research components focusing on acceptability and potential barriers such as stigma around tuberculosis and its association to HIV bring crucial information for future scale-up.

The CONTACT study will bring new evidence of alternative ways for tuberculosis contact management in a more convenient manner for children and their families with an expected impact on TPT uptake, treatment completion, and increase of case detection.

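### The abstract, objective and 60% planning rate refer to children eligible for TPT, but the primary endpoint counts all declared children, so the label is wrong and power may be overstated

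*Protocol article*

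**What the plan says.** The protocol article describes the primary population in two ways.

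- **Eligible children.** The abstract says "The primary endpoint is the proportion of eligible child contacts who initiate and complete the preventive therapy". Earlier in the same paragraph it describes eligible children as those under 5 years "or older (5–14 years) child contacts living with HIV, and with no evidence of TB disease". The primary objective (Study objective and endpoints) is "to compare the proportion of household child TB contacts eligible for TPT who initiate and complete TPT" under the two models. The Sample size calculation gives its 60% control rate for eligible children.
- **Declared children.** The endpoint sentence that follows the objective takes children in the age and HIV groups "who are declared by the index case and who initiate and complete the TPT", with no exclusion of TB disease. The Primary analysis section agrees: "The denominator for the analysis of the primary endpoint is the number of child contacts" in those groups as declared at the inclusion visit.

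The Sample size calculation mixes the two. Its target of 1500 is first a number of declared children who would be eligible, and then becomes "With a minimum of 1500 enrolled child contacts".

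Table 1 places the exclusion of TB disease after declaration and screening. The first sensitivity analysis takes children identified at screening, again without removing those with TB. The per-protocol analysis is not said to remove them either.

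**The concern.** A declared child found to have TB is put on TB treatment and does not go on to initiate and complete TPT. Under the stated denominator that child is a non-success, although the care pathway worked as intended and the article describes the study "with an expected impact on TPT uptake, treatment completion, and increase of case detection".

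Two things are at stake. A result reported as the proportion of eligible children would not be the quantity computed. And a control rate and effect size assumed for eligible children do not carry over unchanged to a denominator that includes children with TB, so the stated power may be too high.

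**Working it through.** **Inputs from the protocol article.** 1500 children, 20 clusters, 1:1 allocation, 60% versus 70%, intra-cluster correlation (ICC) 0.01, coefficient of variation (CV) of cluster size 0.5, stated power 85% (Sample size calculation and abstract). TB prevalence: the Background cites a meta-analysis in which "10% of young child contacts had TB disease at the time of screening".

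**Assumptions.** TB prevalences of 2%, 5% and 15%, and all screening shares, are assumptions. Alpha is taken as 0.05 two-sided. The article prints 0.05% and no sidedness; read literally (0.0005), power would be about 29%.

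**Step 1: reproduce the stated power.**
- Mean cluster size m = 1500/20 = 75.
- Design effect = 1 + ((CV² + 1)m − 1) × ICC = 1 + (1.25 × 75 − 1) × 0.01 = 1.9275.
- Effective n per arm = 750/1.9275 = 389.1.
- Power = Φ{[d√n − 1.96√(2p̄(1 − p̄))] / √(p₀(1 − p₀) + p₁(1 − p₁))}, where d = p₁ − p₀ and p̄ is the mean of p₀ and p₁.
- For 60% versus 70%: (1.973 − 1.322)/0.671 = 0.970, so power is 83.4%. This is within 2 points of the stated 85%.

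**Step 2: move the rates to the declared denominator.** Suppose 60% versus 70% holds among TB-free children, prevalence t is equal in the two arms, and no child with TB completes TPT. Each rate, and so the difference, is multiplied by (1 − t). The effective n is unchanged.

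| TB prevalence t | Facility | Community | Difference (points) | Power |
|---|---|---|---|---|
| 0 (plan) | 60.0% | 70.0% | 10.0 | 83.4% |
| 2% | 58.8% | 68.6% | 9.8 | 81.3% |
| 5% | 57.0% | 66.5% | 9.5 | 77.9% |
| 10% (cited) | 54.0% | 63.0% | 9.0 | 72.2% |
| 15% | 51.0% | 59.5% | 8.5 | 66.5% |

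At 10%: (1.775 − 1.366)/0.694 = 0.590, so power is 72.2%. The article's claim of at least 80% power covers control rates from 60% to 70%; 54% lies below that range.

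**Step 3: is one arm penalised?** Take t = 10% and assume 65% of declared children are screened in the facility arm and 85% in the community arm.
- Detected TB, as a share of declared children: 0.10 × 65% = 6.5% and 0.10 × 85% = 8.5%.
- TB in unscreened children, also non-successes: 0.10 × 35% = 3.5% and 0.10 × 15% = 1.5%.
- Total: 10% in each arm.

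With no true effect in TB-free children, the difference on the declared denominator is 0.

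**Step 4: would a denominator set after screening be better?** Use the same inputs with no true effect and 60% completion among TB-free children, so that 0.90 × 60% = 54% of declared children complete in each arm.
- Removing detected TB only: 54/93.5 = 57.8% versus 54/91.5 = 59.0%, a spurious +1.3 points before rounding.
- Keeping only screened and cleared children: 54/58.5 = 92.3% versus 54/76.5 = 70.6%, a spurious −21.7 points.

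The declared denominator avoids both distortions because it is fixed before contact screening.

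**The case against.** The strongest reply is that the operative text is consistent. The Methods endpoint and the analysis denominator both use declared children, and eligible can be read as shorthand for the age and HIV groups. The Community-based model section supports this: it lists being asymptomatic as a condition separate from eligibility, which it then spells out by age and HIV status alone. On that reading the 60% may already refer to declared children, and no power is lost. This stands as a possible reading, but the abstract's own definition contradicts it, so the text has to be settled either way.

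A second reply is that the power statement concerns a 10-point difference in the primary outcome itself. If that difference is kept and only the control rate falls to 54%, then 54% versus 64% gives (1.973 − 1.363)/0.692 = 0.881 and power of 81.1%. Most of the loss in the table therefore comes from the shrunken difference and depends on the effect having been set among eligible children.

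Third, TB detection has its own secondary cascade in Table 1, analysed with a similar model, so that benefit is reported. This is correct, and it is why a combined outcome belongs in a supportive role only.

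A reader might also infer a stronger claim: that the arm that screens more finds more TB and so collects more failures, biasing the effect towards the null. With assumed screening of 95% versus 70%, detected TB is 9.5% versus 7.0%. But missed TB is 0.5% versus 3.0%, and those children fail too, so the total is again 10% in each arm. The 2.5-point gap in detected cases separates two different endpoints and is not a bias in the planned one.

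**Conclusion.** The population is stated inconsistently, and this should be corrected. The primary proportion as computed is among declared children, not among eligible children as the abstract and objective say. If the planning rates apply to TB-free children, the difference shrinks from 10 to 9 points at 10% TB, and power falls from about 83% (85% as stated) to about 72%. Over assumed prevalences of 2% to 15%, power runs from about 81% to 67%.

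These figures rest on equal TB prevalence in the two arms, on a background prevalence that is not a planning value for this trial, and on no child with TB completing TPT. A screened child whose TB was missed could complete TPT and count as a success. That would soften the shrinkage, and it could create an arm difference if it happened more often in one arm. Both models use the same symptom list, and the article gives no figure for missed TB. The documents therefore do not support a claim of arm-specific bias, nor a case for abandoning the declared denominator.

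**What to change.** 1. Keep declared children as the primary denominator. Use that term in the abstract, the objective and the 1500 target, in place of eligible and enrolled.
2. Restate the control rate, the target difference and the power on that denominator, with the assumed TB prevalence. State that a declared child diagnosed with TB or with a contraindication to TPT counts as not having completed TPT.
3. Add one pre-specified supportive analysis with the same model and denominator, counting as success either TPT completed, or TB diagnosed and TB treatment started. Describe it as a different estimand, not as a bias correction.
4. Apply the Study population exclusion of contacts already on TPT or TB treatment to the denominator only where that status is ascertained at the index-case inclusion visit in the same way in both arms. Removing children on information learned at screening would bring back selection that depends on arm.

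The cost is changes of wording, one recalculation and one extra model. TB diagnosis and start of TB treatment are already Table 1 endpoints; only the pre-enrolment treatment status in item 4 may need a check that the inclusion visit records it.
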